## Objective

The primary objective of this trial is to evaluate the clinical effectiveness of the automated pneumatic ventilation (APV) method in prehospital resuscitation of out-of-hospital cardiac arrest (OHCA) compared to the bag-valve-mask (BVM) method. The primary outcome is any return of spontaneous circulation (ROSC).

The secondary objectives include:

1. Comparing the ventilation parameters between the APV and BVM methods.
2. Evaluating the overall resuscitation quality in the APV and BVM groups.
3. Comparing the satisfaction levels of emergency medical technicians between the APV and BVM groups.

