## Randomization and blinding

The participating EMS teams will be divided into two randomized clusters. Each cluster will be assigned to either the APV or BVM group. The duration of a cluster is 14 days (two weeks). The study center will instruct the clusters to alternate between APV and BVM according to a sequence determined by random allocation.

The randomization process was done by a research assistant. The sequence was generated using tool by Sealed Envelope Ltd. 2022 [20]. The formula this program used is based on the textbook *Clinical Trials: A Practical Approach* [21]. In the program, the seed is generated by a random table by Microsoft Excel. Each block contains 6 clusters. However, the EMTs are not aware of the randomization and allocation method.

The allocation sequence will be revealed until three days before the next cluster begins via social network application.

Blinding of the EMTs or hospital staff is not feasible because the ventilation equipment used in the study cannot be blinded

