## Outcome measurement

- - 1. Primary outcome

The primary outcome of the trial is any ROSC (defined as prehospital ROSC or ROSC achieved after in-hospital resuscitation).

- - 1. Secondary outcomes

The secondary outcomes include the following:

- Prehospital ROSC: ROSC before hospital arrival
- 24-hour survival
- Survival to discharge
- Neurological function on discharge
- Ventilation rate in prehospital resuscitation
- Tidal volume in prehospital resuscitation
- End-tidal CO2 level in prehospital resuscitation
- Chest compression fraction in prehospital resuscitation
- Intravenous catheter insertion in prehospital resuscitation
- Epinephrine injection in prehospital resuscitation
- Satisfaction of EMT in prehospital resuscitation (Appendix 2)

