## Study procedures and workflow

- - 1. Weekly Group Assignment Announcement

Every Friday evening, the group allocation results are announced via the study group's communication app. If assigned to the intervention group, the paramedics must ensure that the APV device is functioning properly and place it in the ambulance. If allocated to the control group, the device should be removed from the ambulance. The new round of group allocation will begin on Monday at 8 AM.

- - 1. OHCA rescue

When the dispatch center reports an OHCA case, an OHCA is identified on scene, or a patient experiences cardiac arrest during transportation to the hospital, the EMTs will confirm whether the case meets the inclusion criteria. The EMTs will then perform ACLS and determine which advanced airway (ETT or SGA) to use based on the situation at the scene.

The standard ACLS procedure in Hsin-chu county is provided in Appendix 1.

- - 1. Device Setup After Establishing Advanced Airway

After establishing the advanced airway (SGA or ETT), the following equipment should be connected under the following sequence:

Patient → Endotracheal tube or supraglottic airway → HEPA filter → AccuVent sensor → End-tidal CO2 sensor → Automatic ventilator → Oxygen tank (Figure 1).

- - 1. Data Entry After Rescue

After completing the rescue, upon returning to the fire department, the EMT should log the case data into an Excel form and upload the rescue reporting form. Additionally, they should complete the satisfaction questionnaire after every successful patient recruit.

These data are stored in a secure database.

- - 1. Data Export from Zoll X-series

A designated staff member will export the case’s ventilation and chest compression physiological data from the Zoll X-series monitor and then upload to a secured database.

Figure 2. Equipment connection for enrolled OHCA patients.

[figure not shown]

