# Analytic Plan

Statistical Package for the Social Sciences (version 26.0; IBM Corp., Armonk, NY, USA) will be used for the statistical analyses in this study. Intention to treat analysis will be adopted for comparing outcomes between interventions. Firstly, descriptive statistics of demographics (Table 1), ventilation parameters (Table 2), and outcomes (Table 3) among APV group and BVM group will be presented as number (percentage) for categorical variables and median (interquartile range) for continuous variables. Categorical variables will be compared using Pearson’s chi-square test or Fisher’s exact test, while continuous variables will be compared using Mann–Whitney U test. Secondly, multivariable logistic regression will be conducted to investigate the association of different ventilation interventions and patients’ outcomes, adjusting for potential confounders. Subgroup analysis, presented as a forest plot, will also be performed to investigate the impact of different interventions on outcomes in different subgroups. We will also compare the adjusted absolute difference between ventilation parameters measured in the APV and BVM group using the linear mixed-effects model (LMM). For the LMM, variables including demographics, prehospital information, resuscitation managements were included as fixed effects, whereas each patient will be modeled as a random effect. Two tail p-values <0.05 will be considered as statistically significant and will be corrected with Bonferroni correction in post-hoc analyses.

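### Repeated EMT satisfaction ratings, made by teams that use both devices, have no analysis in the protocol that accounts for the rater

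*Protocol*

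**What the plan says.** The Objective section gives three secondary objectives, the third being "Comparing the satisfaction levels of emergency medical technicians between the APV and BVM groups". Outcome measurement lists EMT satisfaction as a secondary outcome and refers to Appendix 2 for the instrument, which is not in the text at hand.

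Under Study procedures and workflow (data entry after rescue), the instruction to EMTs is that "they should complete the satisfaction questionnaire after every successful patient recruit". Under Randomization and blinding, a cluster lasts 14 days and "The study center will instruct the clusters to alternate between APV and BVM according to a sequence determined by random allocation". The workflow section matches this: the APV device is put into or taken out of the ambulance according to the allocation.

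The Analytic Plan gives general rules by type of variable: "Categorical variables will be compared using Pearson’s chi-square test or Fisher’s exact test", "while continuous variables will be compared using Mann–Whitney U test". It adds a logistic regression for patients' outcomes and a linear mixed model for ventilation parameters in which the patient is the random effect. No EMT, team or period term appears. Satisfaction is not named in that section, and dummy Tables 1 to 3 do not list it.

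**The concern.** For this outcome the respondent is the EMT, not the patient. Some people score leniently and others strictly, so forms from one rater resemble each other. A test that treats all forms as coming from different people then has the wrong standard error. The direction of the error depends on how each rater's forms divide between the devices:

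- If a rater scores both devices, rater leniency largely cancels in the comparison, but an independent-samples test leaves it in the error term.
- If a rater scores mainly one device, leniency is confounded with device and the independent-samples test understates the uncertainty.

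At stake is the reading of one of three secondary objectives: a real preference could be missed, or a few frequent raters could produce an apparent one.

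**Working it through.** **1. The plan's own figure.** The protocol states no sample size, SD, effect or correlation for satisfaction. Its only sample size is for any ROSC. Proportions of 0.567 and 0.433, two-sided alpha 0.05 and power 0.80 give 218 per arm, 436 in all. With design effect 1 + (3 − 1) × 0.06 = 1.12, 436 × 1.12 = 488.3 (stated 488), and 488 / 0.95 = 513.7, so 514. These reproduce. They serve here only to suggest the number of forms.

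**2. Do ratings repeat?** At team level, yes. Taking 3 patients per cluster, 514 / 3 ≈ 171 cluster-periods. June 2023 to December 2025 holds about 67 fortnights, and 171 / 67 ≈ 2.6 clusters at a time. Teams would therefore change device many times. The protocol does not say how many EMTs there are, who in the crew fills in the form, or how cases spread over individuals.

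**3. Which stated method could apply?**
- Satisfaction treated as continuous: Mann–Whitney, by the general rule.
- Satisfaction treated as categorical: chi-square or Fisher, by the general rule.
- The mixed model is limited to ventilation parameters, and its patient effect cannot stand in for a rater.

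Both general routes assume independent forms.

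**4. Size, on assumed inputs.** Assumptions, none from the protocol: 480 forms, 240 per arm; total SD 1; true difference 0.25 SD; normal scores; within-rater correlation ρ of 0.1, 0.3 or 0.5.

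Formula for raters who score both devices equally often: power = Φ(0.25 / SE − 1.96).
- Rater ignored: SE = √(2/240) = 0.0913, power 78%.
- Rater accounted for: SE = √(2(1 − ρ)/240) = 0.0866, 0.0764 and 0.0645, giving power 82%, 91% and 97%. The effective sample size rises by 1/(1 − ρ) = 1.11, 1.43 and 2.0.

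Simulation, 2,000 runs per setting, with 60, 120 or 240 raters (ranges are over these). Mann–Whitney is compared with a random-intercept model for EMT with known variances:

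| How an EMT's forms divide | ρ | Mann–Whitney type I error | Mann–Whitney power | EMT model power |
| --- | --- | --- | --- | --- |
| Equally between devices | 0.1 | 4% | 77–79% | 82–83% |
| | 0.3 | 2–3% | 80–81% | 91–92% |
| | 0.5 | 0.4–0.9% | 83–84% | 97–98% |
| At random | 0.1 | 5–6% | 75–76% | 77–80% |
| | 0.3 | 5% | 75–77% | 82–88% |
| | 0.5 | 5% | 75–76% | 89–95% |
| One device only | 0.1 | 8–14% | not valid | no gain |
| | 0.3 | 13–28% | not valid | no gain |
| | 0.5 | 16–37% | not valid | no gain |

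Type I error of the EMT model stays between 3.9% and 5.9% throughout. With random exposure, the setting-by-setting power loss is 2.4 to 3.7 points at ρ = 0.1, 6.5 to 11.8 at 0.3 and 13.9 to 19.2 at 0.5.

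**5. Check on the last rows.** With one device per rater and forms falling at random on raters, the variance is inflated by about 1 + m̄ρ, where m̄ is the mean number of forms per rater.
- 60 raters, ρ = 0.5: m̄ = 8, inflation 5, type I error 2(1 − Φ(1.96/√5)) ≈ 38%, against 37% simulated.
- 240 raters, ρ = 0.1: m̄ = 2, inflation 1.2, type I error 2(1 − Φ(1.96/√1.2)) ≈ 7%, against 8% simulated.

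**The case against.** The Analytic Plan never mentions satisfaction. A reader might infer that the protocol prescribes Mann–Whitney for it, but that follows only if the score is continuous, and the instrument in Appendix 2 is not available. The test for a late-listed, unpowered secondary outcome is also something a separate analysis plan may settle. This stands as far as it goes: no particular test can be attributed to this outcome. It does not remove the point, because the Analytic Plan does more than stay silent. It fixes two-sample rules for both types of variable and confines its mixed model to other data, so satisfaction falls under a test that ignores the rater whichever type it is. A rater code also has to be collected at the time, which a later analysis plan cannot arrange.

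A second tempting reading is that the trial certainly loses power it could have had at no cost while holding 5% type I error. The documents do not support it. Alternation is shown for teams, not for individual EMTs, and with about 3 patients per cluster some EMTs may rate few cases or only one device. The type I error then rises instead. The gain also requires a rater identifier. The variables listed under Data Collection and Follow-up include none, although the form itself may carry one.

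**Conclusion.** The point holds in a limited form. The forms are repeated measurements by teams exposed to both devices, and none of the stated methods that could cover them takes account of that. The standard error will be wrong unless within-rater correlation is negligible: too large, or simply inefficient, if raters cross between devices, and too small if individual exposure is lopsided.

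The size is illustrative only. It rests on the assumed number of forms and raters, the 0.25 SD difference and the correlation. With random exposure, the power loss is a few points at a correlation of 0.1 and about 14 to 19 points at 0.5. With one device per EMT, the type I error is 8% to 37%. The simulation has no 14-day cluster effect and treats the variances as known, so it shows the effect of the rater alone and not the exact performance of the model proposed below. This is a minor matter on a secondary outcome and does not affect the primary ROSC conclusion.

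**What to change.** Add a sentence to the Analytic Plan: EMT satisfaction will be analysed with a linear or ordinal mixed model (according to the scale), with arm as fixed effect and random intercepts for EMT and for the 14-day cluster-period. Use team in place of EMT if the form is completed by the crew or no EMT code exists. Make sure that each form carries a coded rater or team identifier. A rank test stratified by EMT (van Elteren) can serve as a non-parametric check where raters have scored both devices.

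The cost is one coded field on a form that is already completed and slightly more analysis work. Forms already collected without an EMT code can be analysed with team as the grouping factor, which recovers only part of the within-rater information.

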# Sample Size Estimation

In the original version of sample size calculation, we chose a secondary outcome (ventilation rate) to be the reference to calculate the sample size. Because we couldn’t find any studies with a similar trial design and primary outcome as our study. The original sample size was 260 patients. However, in August 2024, we identified some comparable studies to guide our calculations more precisely.

We chose the pilot study by Shin et al., which compared automatic mechanical ventilation (MV) with manual bag ventilation (BV) during CPR [19]. In that study, the primary outcome, any ROSC, was achieved in 56.7% of the MV group and 43.3% of the BV group—values closely aligning with our expected ROSC rates. Thus, we conducted an initial power analysis in G*Power 3.1 using the following parameters: Z test family, difference between two independent proportions, two-tailed test, proportions of 0.567 and 0.433, alpha of 0.05, power of 0.8, and equal allocation (1:1). This analysis suggested 218 patients per arm, totaling 436.

To account for the clustering effect due to randomization at the EMS team level, we included an intraclass correlation coefficient (ICC). Our EMS teams are expected to recruit 3 patients per cluster (over 14 days). Given the substantial variability in OHCA patient conditions, we assumed a low ICC of 0.06. The design effect was therefore calculated as 1+(3−1) ×0.06=1.12, adjusting our sample size to 488. Finally, with an estimated 5% dropout rate, the final required sample size was increased to 514 patients.

Figure 3. Sample size calculation by G*Power 3.1

[figure not shown]

# Data and Safety Monitoring Boards and Interim Analysis

This study has established a Data and Safety Monitoring Board (DSMB) in accordance with the standards of the National Institutes of Health (NIH). The DSMB will review the completeness of the data and monitor for any obvious abnormalities that could compromise the patients' safety every six months. Additionally, when enrollment reaches half of the target sample size (130 participants), the board will independently conduct an interim analysis. If any concerning situations arise, the board will consult with the principal investigator to determine whether the study should be suspended. The DSMB meetings will be held every six months.

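### The interim is set at half of the target and at 130 participants, but the target is now 514, so the two triggers conflict (257 against 130)

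*Protocol*

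**What the plan says.** In the protocol, Data and Safety Monitoring Boards and Interim Analysis states that "when enrollment reaches half of the target sample size (130 participants), the board will independently conduct an interim analysis".

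Sample Size Estimation gives two targets. The first was based on ventilation rate: "The original sample size was 260 patients". The second is the result of a recalculation in August 2024 based on any ROSC: "with an estimated 5% dropout rate, the final required sample size was increased to 514 patients".

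Interim analysis and stopping criteria attaches a decision to the look. If a chi-square test on ROSC events gives p<0.05, the study may be terminated. The Analytic Plan keeps two-sided 0.05 as the significance threshold for the trial. The working plans list an interim analysis under both 2024 and 2025, but the month marks cannot be read.

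**The concern.** The words of the trigger (half of the target) and its number (130) agreed when the target was 260. They no longer agree at 514. The likely explanation is that the sample size section was updated and the monitoring section was not. Both are current text.

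The trigger fixes when the board may look at the primary outcome with a rule that can end the trial. With two triggers in one sentence, the board could follow either, and the choice could be made after data exist. The two readings are far apart: one look falls at a quarter of planned enrolment, the other at half. They differ in the size of difference needed to cross the boundary, in the chance of crossing it under the planned effect, and in the fraction to which any alpha adjustment would have to be tied.

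**Working it through.** **Inputs.** From Sample Size Estimation: ROSC proportions 0.567 and 0.433, two-tailed alpha 0.05, power 0.80, 1:1 allocation, 3 patients per cluster, ICC 0.06, 5% dropout, targets 260 (old) and 514 (current). From the monitoring section: trigger 130. From the stopping criteria and the Analytic Plan: p<0.05 at the interim and at the end.

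**Step 1: reproduce the current target.** The mean proportion is 0.5.
- Per arm: n = [1.96·√(2·0.5·0.5) + 0.842·√(2·0.567·0.433)]² / 0.134² = 217.4, rounded up to 218. Total 436, matching "This analysis suggested 218 patients per arm, totaling 436".
- Design effect: 1 + (3−1)·0.06 = 1.12, and 436 × 1.12 = 488.3, stated as 488.
- Dropout: 488/0.95 = 513.7, rounded up to 514.

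The target of 514 reproduces exactly, so it is not in doubt.

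**Step 2: the fraction.**
- 130/260 = 50.0%
- 130/514 = 25.3% (130/488 = 26.6% of the number before the dropout allowance)
- 514/2 = 257

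**Step 3: difference needed for p<0.05 at the look**, with rates near 50%: 1.96·√(2·0.25/n per arm).
- At 130 (65 per arm): 1.96·√(0.5/65) = 0.172, or 17.2 points. With the design effect: 0.172·√1.12 = 0.182, about 18 points.
- At 257 (128.5 per arm): 1.96·√(0.5/128.5) = 0.122, or 12.2 points.

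In whole patients at 65 per arm, 38 against 27 events gives p = 0.054 and 38 against 26 gives p = 0.035. The second is a difference of 12/65 = 18.5 points. The planned effect is 56.7 − 43.3 = 13.4 points.

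**Step 4: power for the planned effect at the look**, as Φ[(0.134 − threshold)/√(2·0.567·0.433/n per arm)].
- At 130: (0.134 − 0.172)/0.0869 = −0.44, giving 33%.
- At 257: (0.134 − 0.122)/0.0618 = 0.19, giving 58%.
- With n divided by 1.12: about 30% and 53%.

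**Step 5: overall type I error**, with 1.96 at both the interim and the final analysis: 1 − P(|Z₁|<1.96 and |Z₂|<1.96), bivariate normal with correlation √t, where t is the interim fraction.

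| Interim at | t | Overall type I error |
| --- | --- | --- |
| 130 of 514 | 0.253 | 9.1% |
| 257 of 514 | 0.500 | 8.3% |

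The timing accounts for about 0.8 points. The rest of the excess over 5% (8.3 − 5 = 3.3 points) remains with the look at 257.

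**The case against.** The best defence is that 130 is history. The Trial Summary schedules the trial from June 2023, the recalculation dates from August 2024, and an interim analysis is listed for 2024. The look may have been done at half of the old target before the target changed. Alternatively, half of the target may be the operative rule and 130 only a leftover parenthesis. Either is possible, but the protocol states neither. The sentence is in the future tense, and nothing says that 130 was kept deliberately or that target there means 260. The conflict therefore stands. What does not stand is a flat statement that the look will happen at 25%.

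Three other stronger readings are tempting and are not supported:

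- **That this is the only planned efficacy look.** The interim analysis appears under both 2024 and 2025. With the month marks lost, this could be one look spanning the year end or two separate looks.
- **That a stop at 130 would need an implausibly large difference.** The threshold of 17.2 points lies (17.2 − 13.4)/8.7 = 0.44 standard errors above the planned effect and would be crossed about a third of the time if the plan is right. The fair statement is that a stop there would tend to overestimate the effect.
- **That the stale number causes the alpha inflation.** It adds about 0.8 points. Most of the inflation comes from the unadjusted 0.05 rule, a separate defect that moving to 257 does not cure.

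It is also fair to say that the rule is permissive. The study may be terminated rather than must be, and the board consults the principal investigator when concerns arise. That softens the consequence but does not settle when the look takes place.

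**Conclusion.** The point holds as a contradiction in current text. With a target of 514, half is 257, and 130 is 25.3%. Because a possible stop on the primary outcome hangs on this look, the number is a decision figure and not a clerical detail.

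If 130 governs, the look has about 33% power for the planned effect instead of about 58% (30% and 53% with the design effect). Crossing the boundary needs about 17 points observed (about 18 with the design effect) against a planned 13.4. The added type I error is minor.

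These sizes assume equal arms at the look, the protocol's own ROSC rates, the normal approximation, and one interim plus one final analysis, each at two-sided 0.05. The type I error figures take no account of clustering. The contradiction itself needs none of these assumptions. Which trigger is operative, and whether a look has already been made, cannot be determined from the protocol.

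**What to change.** First state in the monitoring section whether an interim analysis of ROSC has been done, and if so when and at how many participants.

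- **If none has been done:** replace 130 participants with 257 participants (half of 514), and tie any alpha boundary to that fraction.
- **If the 130-patient look was done under the old target:** record it as a look at about 25% of the current target, state whether another follows at 257, and account for every look in the final significance level.

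In either case, make the 2024 and 2025 working plan entries agree with the number of looks intended.

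The first case costs one number in a protocol amendment, plus the same correction in any board document that repeats it. The second costs somewhat more, because the final significance level has to be recalculated for the looks actually made. Neither needs additional patients merely to correct the trigger. The unadjusted 0.05 rule needs its own correction.
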